### The LIGHT-ACD trial

#### Objectives

The primary and secondary objectives of the LIGHT-ACD trial are to compare blood pressure changes and blood pressure control between different initial antihypertensive regimens, respectively.

#### Trial design and setting

The LIGHT-ACD trial is an individually randomized trial conducted in the intervention sites of the LIGHT trial. In this nested trial, patients are randomized to receive various initial antihypertensive therapies, and blood pressure changes/control rates between different regimens are compared (Fig. 1).

#### Recruitment of patients

The patients at the intervention sites of the LIGHT trial are eligible if they have a measured baseline SBP ≥140 mmHg and are taking 0–1 class of antihypertensive medication. Key exclusion criteria include diabetes mellitus and intolerance to at least one of the four classes of antihypertensive medications (Table 1). The eligible patients in the LIGHT-ACD trial are categorized into 2 subpopulations. Patients with an SBP of 140–159 mmHg who are not taking any antihypertensive medication are categorized as Population 1, the remainder as Population 2.

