#### Eligibility criteria

In each city-based stage, local coordination centers of the trial invite all primary care sites in their network to participate in the trial. Primary care sites with hypertension clinics are eligible to be included if (1) at least one agent from each of the four classes of antihypertensive medication is available for the prescription [angiotensin-converting enzyme inhibitors (ACEI)/angiotensin receptor blockers (ARB), beta-blockers, calcium channel blockers (CCB), diuretics]; (2) an electronic health record (EHR) is being used for hypertension management providing a structured template for collection of patient data; and (3) at least 100 patients with hypertension are routinely being seen. Cluster drop-out is not expected but might occur if sites voluntarily withdraw during the trial.

Residents aged ≥18 years registered for hypertension treatment at the primary care sites are eligible for the LIGHT trial if they are taking 0–2 classes of antihypertensive medication. Major exclusion criteria include (1) history of coronary heart disease, heart failure, or chronic kidney disease; or (2) intolerance to 2 or more classes of antihypertensive medications; (3) systolic blood pressure (SBP) ≥180 mmHg or diastolic blood pressure (DBP) ≥110 mmHg at the screening visit (see detailed inclusion and exclusion criteria in Table 1). The screening of patients can be automatically performed by the customized EHR. As the informed consent for implementing the CDSS is waived in this trial, doctors can check the eligibility of all patients attending their clinics for hypertension management.

**Table 1 Tab1:** Inclusion and exclusion criteria of participants for LIGHT and LIGHT-ACD trials

Criteria	LIGHT	LIGHT-ACD
**Inclusion**	Residents aged ≥18 years registered for hypertension treatment at primary care sites	Participants from intervention sites of LIGHT study with systolic blood pressure ≥140 mmHg at the screening visit
	Taking 0–2 classes of antihypertensive medications	Not taking antihypertensive medication or taking only one which was not beta-blocker
**Exclusion**	History of coronary heart disease^a^, heart failure, and chronic kidney disease	Known/diagnosed diabetes mellitus
	Intolerance to 2 or more classes of antihypertensive medications	Intolerance to 1 or more classes of antihypertensive medications
	Secondary hypertension (physician-diagnosed)	Home blood pressure (if available) below 135/85 mmHg

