	Systolic blood pressure ≥180 mmHg or diastolic blood pressure ≥110 mmHg at the screening visit	
	Serious medical conditions (e.g., malignant cancer and hepatic dysfunction)	
	Currently in an acute episode of disease	
	Currently pregnant or breastfeeding, or planning a pregnant or breastfeeding during the study	
	Cognitive or communication disorders	

^a^ Including angina, myocardial infarction, coronary artery bypass grafting, percutaneous coronary intervention, >50% stenosis of coronary artery, or positive stress test

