#### Randomization and blinding

Populations 1 and 2 are randomized to different antihypertensive regimens separately. Minimization randomization [26] is used to ensure the balancing of age, gender, and education level among different arms. The allocation is centrally performed and concealed within the CDSS. Neither doctors nor patients are blinded to treatment allocation. Population 1 individuals are randomized to receive one of the initial monotherapies of A (ACEI or ARB), C (CCB), or D (diuretics). If additional treatment is needed, they are further randomized to add either C or D, so patients initiated with A follow either A-AC-ACD or A-AD-ADC with C and D as the add-on medications, respectively. The randomization of drug regimen among patients initiated with C or D is similar to patients initiated with A. Population 2 individuals are randomized to receive one of the three initial dual therapies of AC, AD, or CD. Subsequently, D, C, or A are added to achieve blood pressure control, if necessary, respectively (Fig. 1).

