#### Outcomes

The primary outcome is the difference in the change in blood pressure from baseline to 9 months between different drug regimens of initial therapy. Secondary outcomes include the proportion of individuals with blood pressure controlled at 9 months; the proportion of individuals with SBP <160 mmHg and DBP <100 mmHg at 9 months; the proportion of individuals who received monotherapy (only in Population 1), dual therapy, triple therapy, and referral at 9 months; the proportion of individuals reported to have antihypertensive drug-related side-effects; and the proportion of individuals transferred to usual care for any reasons. The exploratory outcome is the change in blood pressure from baseline to 9 months of six protocols embedded in the CDSS (Table 2).

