#### Statistical analysis

All the intervention evaluations will be performed on an intention-to-treat basis. Multiple imputations by chained equations will be used to account for missing values.

Patient characteristics will be summarized by comparison group and tested for differences using *t*-tests and chi-square tests. To assess the effectiveness of each initial antihypertensive regimen and protocol, we will estimate a mixed-effects generalized linear model for each outcome including indicators for treatment groups, baseline blood pressure, and imbalanced patient characteristics. Additionally, we will perform pre-specified subgroup analyses of outcomes by age, sex, education, smoking status, and tertiles of baseline blood pressure. Considering potential crossovers among treatments, we will also assess the heterogeneity of the treatment effect among per-protocol populations.

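### Population 2 pools untreated patients with patients already on one drug, so the pooled AC, AD and CD contrast is not a comparison of initial dual therapy alone

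*Protocol article*

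**What the plan says.** **Who enters.** Under Recruitment of patients, LIGHT-ACD patients "are eligible if they have a measured baseline SBP ≥140 mmHg and are taking 0–1 class of antihypertensive medication". Table 1 adds the condition "Not taking antihypertensive medication or taking only one which was not beta-blocker". The LIGHT exclusion of "Systolic blood pressure ≥180 mmHg or diastolic blood pressure ≥110 mmHg at the screening visit" carries over, because LIGHT-ACD recruits from LIGHT participants at intervention sites.

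**How they are split.** "Patients with an SBP of 140–159 mmHg who are not taking any antihypertensive medication are categorized as Population 1, the remainder as Population 2".

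**What they are assigned.** "Population 2 individuals are randomized to receive one of the three initial dual therapies of AC, AD, or CD" (Randomization and blinding). The balancing rule is: "Minimization randomization [26] is used to ensure the balancing of age, gender, and education level among different arms".

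**What is compared.** "The primary outcome is the difference in the change in blood pressure from baseline to 9 months between different drug regimens of initial therapy" (Outcomes). The LIGHT-ACD Objectives and the closing paragraph of the Discussion also speak of initial regimens.

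**How it is analysed.** The model contains treatment group, baseline blood pressure and any patient characteristics found to be unbalanced. Further, "we will perform pre-specified subgroup analyses of outcomes by age, sex, education, smoking status, and tertiles of baseline blood pressure". Treatment at entry appears neither among the balancing factors nor among these subgroups. The parent LIGHT trial does list antihypertensive medication use as a subgroup.

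**The concern.** The word *initial* suggests that each arm shows what happens when a dual regimen is started. In Population 2 that is so only for patients untreated at entry. A patient already on C has a baseline that includes the effect of C. For that patient AC amounts to adding A, CD amounts to adding D, and AD appears to mean giving up C for two other drugs. These are different treatment changes measured from an on-treatment baseline.

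Already-treated patients also qualify only because SBP is still at least 140 mmHg on their current drug, so on average they respond somewhat less well than usual to that class. An arm that keeps the class keeps the weaker response, and an arm that replaces it does not. The pooled contrast may then partly reflect what local doctors had prescribed before the trial. A reader who takes it as the answer for patients starting treatment could carry it to a group in which the regimens compare differently.

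**Working it through.** **1. The plan's own figure.** Sample size gives about 2100 participants with complete follow-up, 75% of them in Population 2, SD 10 mmHg, α = 0.017 and 80% power. Per arm: 2100 × 0.75 / 3 = 525. Detectable difference = (2.387 + 0.842) × 10 × √(2/525) = 1.99 mmHg, which matches the stated 2 mmHg. (Cutting to 420 per arm and reducing the SD to 10 × √0.8 = 8.94 gives the same figure.) The power statement is not in dispute. It supplies the yardstick.

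**2. Composition of Population 2.** Eligibility is SBP ≥140 on zero or one class, with SBP ≥180 excluded. Removing untreated 140–159 leaves (a) untreated 160–179 and (b) one non-beta-blocker class, 140–179.

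**3. Meaning of each assignment by entry treatment.** *Replace* is inferred from the assignment to a named pair.

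| At entry | AC | AD | CD |
|---|---|---|---|
| None | start two | start two | start two |
| A | add C | add D | replace A |
| C | add A | replace C | add D |
| D | replace D | add A | add C |

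**4. Effect on the contrast.** Suppose the classes have equal, additive effects, so that the three arms do not differ in untreated patients. Let the current drug work g mmHg less well than average in patients selected for SBP ≥140. The arm that replaces it gains g relative to the arms that keep it. With T the treated share of Population 2, and pC and pD the shares of treated patients on C and D:

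extra SBP fall of AD over AC = T × g × (pC − pD).

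It is zero when pC = pD, and all three contrasts are unaffected when the three classes are equally common.

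**5. Inputs not in the documents (assumptions).** T = 0.70–0.90; among the treated, C 50–60%, A 35–40%, D 5–10%. The range for T is plausible. If untreated patients at 160–179 are no more numerous than those at 140–159 (25% of the total), at least 50/75 = 67% of Population 2 is already treated. The multiplier T × (pC − pD) runs from 0.70 × (0.50 − 0.10) = 0.28 to 0.90 × (0.60 − 0.05) = 0.495.

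**6. Size of g from selection alone.** This was simulated with assumed untreated SBP of mean 150 and SD 14, mean response to one drug 9 mmHg, noise SD 8, and on-treatment SBP kept if 140–179. Here g is the mean response minus the mean response among those kept.

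| Between-patient SD of response | g (mmHg) | AC v AD shift = g × 0.28 to g × 0.495 |
|---|---|---|
| 3 | 0.40 | 0.1–0.2 |
| 5 | 1.07 | 0.3–0.5 |
| 7 | 1.99 | 0.6–1.0 |

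**7. Against the test.** The standard error of a pairwise contrast is 10 × √(2/525) = 0.617 mmHg. With no true difference in untreated patients, the chance of p < 0.017 is about 6% for a shift of 0.5 mmHg and 22% for 1.0 mmHg, against a nominal 1.7%.

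**8. Precision by stratum.** If 10–30% of Population 2 is untreated, that is about 53–158 per arm. The detectable difference is 3.228 × 10 × √(2/52.5) = 6.3 down to 3.228 × 10 × √(2/157.5) = 3.6 mmHg. For the already-treated stratum (about 368–473 per arm) it is 2.4 down to 2.1 mmHg.

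**The case against.** **No bias arises.** Population 2 is randomised on its own, centrally and with concealment, and analysed by intention to treat. A reader might infer that the contrast is biased, or that one arm carries an unfair handicap. The documents do not support that: the effect of being assigned AC rather than AD in these patients is estimated validly, and a pragmatic trial may want exactly that quantity. This stands. What is at issue is which question the contrast answers.

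**Initial may mean the first step of the protocol.** The randomisation section describes stepped sequences, and AC, AD and CD are the first step for Population 2. That is a fair reading of the author's intent. It does not help a reader who takes the word to mean starting treatment, which is not what happens to an already-treated patient.

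**Stopping the current drug is not stated.** The Intervention section speaks of advice to add classes, Fig. 1 is not shown, and no sentence says that a drug outside the assigned pair is withdrawn. This stands, so the replacement column above is an inference. If the drug were continued, these patients would be on three classes, and the assignment would still not be initiation of dual therapy.

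**A shift as large as 2 mmHg is not shown.** A reader might suppose that the effect could match the design difference. That needs g of about 4 mmHg (4 × 0.495 = 2.0), twice the largest value that the selection model gives, and that value already assumes a response SD of 7 around a mean of 9.

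**Refusal of switches is not shown either.** The pilot's non-compliance and refusal figures come from 78 visits with mean SBP 131.5 mmHg and concern the system's advice in general. They say nothing about switching.

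**The analysis plan may cover it.** It is not shown, and interaction terms often sit there. However, the article does list its pre-specified LIGHT-ACD subgroups, and entry treatment is not among them. Adjusting for unbalanced characteristics does not answer the point, because a regimen-by-entry-drug interaction remains when entry drug is perfectly balanced.

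**Conclusion.** The point holds as one of estimand and description. By the article's own eligibility rules, Population 2 mixes starting dual therapy with adding to, or apparently replacing, an existing drug, while the result is presented as a comparison of initial regimens. The pooled contrast is valid for assigned regimen in this mixture, and its value may depend on the prior-drug mix.

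The AC v AD shift is about 0.1–1.0 mmHg, up to half of the 2 mmHg design difference. It rests on assumed treated shares, drug mix and response variability, and on equal, additive class effects. It is zero if the three prior classes are equally common. None of these inputs is in the documents, so the range is an illustration. It would be too strong to say that the arms fail to compare initial dual therapies at all: the untreated patients at 160–179 mmHg do give such a comparison.

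**What to change.** 1. Keep the pooled intention-to-treat contrast of AC, AD and CD as the primary analysis of Population 2.
2. Add entry treatment (none, A, C, D) to the Population 2 model as a pre-specified covariate.
3. Add it to the LIGHT-ACD subgroup list, with its interaction with assigned regimen, and report the contrasts separately for untreated and already-treated patients.
4. Describe the pooled result as the effect of assigned dual regimen in patients who were untreated or on one drug at entry, and not as initial therapy alone. State what the protocol does with a current drug outside the assigned pair, so that readers know which comparisons are replacements.

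The cost is wording in the analysis plan and the report. Table 3 shows that current medications are already collected at recruitment. The price is imprecision: on the assumed shares, the untreated stratum alone could detect only 3.6–6.3 mmHg, and the interaction test has (4 − 1) × (3 − 1) = 6 degrees of freedom. These results should be labelled supportive.

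Two other changes are not advised. Adding entry drug to the minimisation would balance it between arms but leave the interaction in place. Restricting the conclusion to untreated patients would give up most of the sample for the imprecise estimate just described.

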#### Randomization and blinding

Populations 1 and 2 are randomized to different antihypertensive regimens separately. Minimization randomization [26] is used to ensure the balancing of age, gender, and education level among different arms. The allocation is centrally performed and concealed within the CDSS. Neither doctors nor patients are blinded to treatment allocation. Population 1 individuals are randomized to receive one of the initial monotherapies of A (ACEI or ARB), C (CCB), or D (diuretics). If additional treatment is needed, they are further randomized to add either C or D, so patients initiated with A follow either A-AC-ACD or A-AD-ADC with C and D as the add-on medications, respectively. The randomization of drug regimen among patients initiated with C or D is similar to patients initiated with A. Population 2 individuals are randomized to receive one of the three initial dual therapies of AC, AD, or CD. Subsequently, D, C, or A are added to achieve blood pressure control, if necessary, respectively (Fig. 1).

#### Treatments

The assignment of treatment is presented as the CDSS recommendation (class and dose). The specific agent within each class is at the doctor’s discretion based on the available medications of the sites. For each case, the titration of antihypertensive medication is performed automatically by the CDSS according to the assigned drug regimens.

#### Outcomes

The primary outcome is the difference in the change in blood pressure from baseline to 9 months between different drug regimens of initial therapy. Secondary outcomes include the proportion of individuals with blood pressure controlled at 9 months; the proportion of individuals with SBP <160 mmHg and DBP <100 mmHg at 9 months; the proportion of individuals who received monotherapy (only in Population 1), dual therapy, triple therapy, and referral at 9 months; the proportion of individuals reported to have antihypertensive drug-related side-effects; and the proportion of individuals transferred to usual care for any reasons. The exploratory outcome is the change in blood pressure from baseline to 9 months of six protocols embedded in the CDSS (Table 2).

#### Sample size

We assume approximately 25% of the LIGHT intervention patients are in Population 1 and 75% in Population 2, with an 80% follow-up rate for the primary outcome. We used estimates from the ALLHAT (Antihypertensive and Lipid-Lowering Treatment to Prevent Heart Attack Trial) for power calculations [18, 27]. For each population, we estimate the detectable difference in SBP between treatment groups across a similar range of the intervention participants and statistical power. We assume that the standard deviation in SBP is *σ* = 10 mmHg and that the within-patient SBP correlation is *R*^2^ = 0.2 with a maximum type I error that is Sidak-corrected for three comparisons, *α* = 0.017 [28]. With the current number of LIGHT sites, we estimate about 2100 eligible LIGHT-ACD participants overall with complete follow-up. Under these assumptions, we estimate that for the comparisons of initial monotherapies of A, C, and D in Population 1, we will have 80% power to detect a difference of 3.5 mmHg in SBP, and for comparisons of dual therapies of AC, AD, and CD in Population 2, we have 80% power to detect a difference of 2 mmHg in SBP.

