### Trial status

Protocol version 4.4 commenced on December 28, 2020. As of May 2021, 94 sites (including 7,656 patients in LIGHT and 494 participants in the LIGHT-ACD trial) have been randomized in 4 stages. Site randomization of Stage 1 was on 21 August 2019, Stage 2 on 4 December 2019, Stage 3 on 1 March 2021, and Stage 4 on 14 April 2021. The implementation of the trial is affected by the outbreak of COVID-19, we have extended the enrolment and follow-up periods appropriately in each stage of the trial. Currently, all sites will complete follow-up by the middle of 2022.

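### The LIGHT-ACD power statement (3.5 and 2 mmHg from about 2,100 completers) is not supported by the 494 participants reported as of May 2021 with all 94 sites randomised

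*Protocol article*

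**What the plan says.** In the protocol article, the Sample size section for LIGHT-ACD gives these planning assumptions:

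- The split is worded as "We assume approximately 25% of the LIGHT intervention patients are in Population 1 and 75% in Population 2".
- Four in five participants are expected to provide the primary outcome.
- The "standard deviation in SBP is *σ* = 10 mmHg", the within-patient correlation is R² = 0.2, and alpha is 0.017 after a Sidak correction for three comparisons.
- The number available is tied to the sites already in the trial ("With the current number of LIGHT sites"). The resulting estimate is given as: "we estimate about 2100 eligible LIGHT-ACD participants overall with complete follow-up".
- From this it claims 80% power for 3.5 mmHg in Population 1 and 2 mmHg in Population 2.

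The Trial status section dates its counts to May 2021 and gives them as follows: "94 sites (including 7,656 patients in LIGHT and 494 participants in the LIGHT-ACD trial) have been randomized in 4 stages". Stage 3 sites were randomised on 1 March 2021 and Stage 4 sites on 14 April 2021. Enrolment and follow-up were extended because of COVID-19, by an unstated amount, and follow-up is to end by mid-2022.

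Under Recruitment of patients, people at the intervention sites "are eligible if they have a measured baseline SBP ≥140 mmHg and are taking 0–1 class of antihypertensive medication". Diabetes and intolerance to any of the four drug classes exclude. Populations 1 and 2 are defined there as subdivisions of the patients who qualify.

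**The concern.** Two numbers in the same article do not fit together. The power claim needs about 2,625 randomised; the status report shows 494, from the same set of sites that the power claim invokes. The article neither explains how the gap will close nor revises the detectable differences.

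The low count also looks like a matter of eligibility and not only of timing. If the two LIGHT arms are of equal size, about 3,828 intervention patients were already enrolled, more than the 2,625 required, yet only about 13% of them had entered LIGHT-ACD. The 25%/75% sentence does not help: as worded, it assigns all LIGHT intervention patients to the two populations, although the entry criteria remove many of them. In the pilot, mean SBP was 131.5 mmHg, below the 140 mmHg entry threshold.

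At stake is the stated sensitivity of the primary comparison in the nested trial. The primary comparison of LIGHT itself is not affected.

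**Working it through.** **Inputs from the documents.** SD 10 mmHg, R² = 0.2, alpha 0.017 (1 − 0.95^(1/3) = 0.01695), power 80%, 25/75 split, 80% follow-up, about 2,100 completers (LIGHT-ACD, Sample size); three initial regimens in each population (Randomization and blinding); 494 and 7,656 patients and 94 sites (Trial status); 1:1 allocation of sites (Allocation).

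**Assumptions.** Equal arms within each population; a two-sided test (stated for LIGHT, assumed here); equal patient numbers in the LIGHT arms.

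**Formula.** Detectable difference = (z[1 − 0.017/2] + z[0.80]) × SD × √(2/n) = 3.229 × 10 × √(2/n), with n completers per arm.

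**Step 1: reproduce the plan.** 2,100 × 0.25 / 3 = 175 per arm and 2,100 × 0.75 / 3 = 525 per arm. The formula gives 3.45 and 1.99 mmHg, with power 81% at 3.5 and 80% at 2 mmHg. In reverse, 171 and 522 per arm are needed, and 3 × 171 + 3 × 522 = 2,079. So the calculation is sound, and the claim rests on the 2,100. Randomised: 2,100 / 0.80 = 2,625, which is 5.3 times 494.

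**Step 2: put in the observed count.** 494 × 0.80 = 395 completers, or 32.9 and 98.8 per arm. The detectable differences are 7.96 and 4.59 mmHg. If R² reduces the variance, multiply by √0.8: 7.12 and 4.11 mmHg. With no dropout at all (and no R² reduction) they are also 7.12 and 4.11. Even with all 494 in a single population (132 completers per arm), the figure is 3.98 mmHg.

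**Step 3: allow for further enrolment.** I assumed Stages 1 and 2 complete, a constant enrolment rate, a cut-off of 1 or 31 May, a window of 3 or 6 months, and 50-80% of sites in Stages 3 and 4. The projected total is then about 565 to 1,430. The top value takes 10%, 10%, 30% and 50% of sites by stage, a cut-off of 1 May (61 and 17 days open) and 184-day windows: share enrolled = 0.1 + 0.1 + 0.3 × 61/184 + 0.5 × 17/184 = 0.346, and 494 / 0.346 ≈ 1,430.

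| Randomised | Completers | Per arm (Pop. 1, Pop. 2) | Detectable (mmHg) | With R² reduction (mmHg) | Power at 3.5, 2 mmHg (no R²) |
|---|---|---|---|---|---|
| 494 | 395 | 33, 99 | 8.0, 4.6 | 7.1, 4.1 | 17%, 16% |
| 988 (doubled) | 790 | 66, 198 | 5.6, 3.3 | 5.0, 2.9 | 35%, 35% |
| 1,430 | 1,144 | 95, 286 | 4.7, 2.7 | 4.2, 2.4 | about 50% each |
| 2,625 (plan) | 2,100 | 175, 525 | 3.45, 1.99 | 3.09, 1.78 | 81%, 80% |

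**Step 4: yield.** 7,656 / 2 = 3,828 intervention patients; 494 / 3,828 = 12.9%. At that yield, 2,625 LIGHT-ACD participants need 2,625 / 0.129 ≈ 20,300 intervention patients. Over 47 intervention sites that is about 433 per site, against 3,828 / 47 ≈ 81 so far.

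**The case against.** The strongest reply is that 494 is an interim count. Enrolment runs for three months after site randomisation and was extended, so Stage 4 had been open for only about two to seven weeks in May 2021. This stands. A reader might infer that the stated differences are already out of reach, but that would present a projection as a fact. What remains is that the yield of about 13% does not depend on how long enrolment stays open, and the optimistic projection still misses both targets.

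A second reply is that 8.0 and 4.6 mmHg are the least favourable figures, since the analysis adjusts for baseline blood pressure. Also fair, which is why the R² column is shown; it narrows the gap without closing it.

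Three further inferences are tempting and are not supported:

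- *That 3.5 and 2 mmHg reproduce only if R² = 0.2 is ignored.* They also reproduce if 2,100 is taken before dropout and R² reduces the variance: 2,100 × 0.8 = 1,680, or 140 and 420 per arm, and √0.8 × 32.29 × √(2/n) gives 3.45 and 1.99. The wording points to completers, but the other reading cannot be excluded by arithmetic. Under it the target is 2,100 randomised, still 4.3 times 494.
- *That every intervention patient was counted as eligible.* The 25%/75% sentence reads that way, but the numbers do not show it: 2,625 / 47 is 56 per site, against about 81 enrolled per site, and 2,625 / 3,828 is 69%. Since Recruitment of patients defines the two populations among eligible patients, loose wording is the likelier explanation.
- *That null results would be presented as equivalence of regimens.* The LIGHT-ACD outcomes and analysis sections make no equivalence or non-inferiority claim.

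**Conclusion.** The concern holds as a mismatch between the stated power and the article's own accrual report. It is not an arithmetic error: the calculation reproduces at 2,100 completers. At the May 2021 count the detectable differences are about 8.0 and 4.6 mmHg (7.1 and 4.1 with R²). At a total of 1,430, the top of the assumed range, they are about 4.7 and 2.7 mmHg (4.2 and 2.4 with R²). Without the R² reduction, power for the stated 3.5 and 2 mmHg runs from 16-17% to about 50% over that range.

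These sizes rest on equal arms, a two-sided test, the planned 25/75 split and 80% follow-up; the 13% yield also assumes LIGHT arms of equal size. The final LIGHT-ACD total is not known from the document, so the size of the shortfall is a range. That the stated differences lack support from observed accrual holds for every case tried.

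**What to change.** In the LIGHT-ACD Sample size section:

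1. Replace about 2,100 with the enrolment expected in each population, projected from observed accrual and dated, and say how many are randomised and how many are expected to complete.
2. Give the matching detectable differences in place of 3.5 and 2 mmHg, and state whether R² = 0.2 enters the calculation and whether the 80% follow-up has already been applied. If 2,100 completers are still expected, explain how the sites already randomised will supply them.
3. Reword the 25%/75% sentence so that its denominator is LIGHT-ACD participants and not all LIGHT intervention patients.

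The cost is one recalculation and a few sentences. The stated detectable differences become less favourable. No extra patients are needed, and no procedure or treatment rule changes.
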